**Methods:**

This 12-month prospective observational cohort study will recruit 200 families of children aged 2 to 17 years at the Asthma Clinic of the Centre Hospitalier Universitaire Sainte-Justine, a tertiary care pediatric hospital in Montreal, Canada. The primary outcome will be adherence to controller medication, measured using the proportion of prescribed days covered during follow-up. Exploratory outcomes will include health care use. The main independent variables will be unmet social needs, scarcity, and future discounting, measured using validated instruments. These variables will be measured at recruitment as well as at 6- and 12-month follow-ups. Covariates will include sociodemographics, disease and treatment characteristics, and parental stress. Primary analysis will compare adherence to controller medication, measured using the proportion of prescribed days covered, between families with versus those without unmet social needs during the study period using multivariate linear regression.

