### Scientific Objectives

The overall aims of this project are to determine whether scarcity and future discounting are associated with medication adherence in children with asthma and to explore their role in the relationship between unmet social needs and adherence. Using a prospective observational study, we will investigate three primary relationships:

The relationship between scarcity, future discounting, and adherence to asthma controller medication;The association between unmet social needs, scarcity, and future discounting; andThe potentially mediating role of scarcity and future discounting on the relationship between unmet social needs and adherence to medication in children with asthma.

Our hypotheses related to each of these three primary relationships are the following:

We hypothesize that individuals experiencing scarcity and those with higher rates of future discounting will have lower adherence to asthma controller medication.We hypothesize that unmet social needs will be related to scarcity and future discounting in the following ways:Parents reporting unmet social needs will be more likely to experience scarcity and have greater levels of future discounting;The number of unmet social needs will correlate with level of scarcity and future discounting; andImprovements in a family’s unmet social needs during the study period will be associated with decreased scarcity and future discounting rates.We expect that scarcity and future discounting will play a mediating role in the relationship between unmet social needs and adherence to medication, with higher levels of both scarcity and future discounting specifically amplifying the impact of unmet social needs on medication adherence.

We will also examine two exploratory aims:

Examine whether adherence to medication mediates the association between unmet social needs and asthma outcomes: asthma control, ED visits, and hospitalizations.Document the progression of unmet social needs as the world moves to the next phase of the COVID-19 pandemic.

This project will help understand the relationship between cognitive factors, medication adherence, and unmet social needs, opening the door to developing targeted interventions to improve adherence to medication and, ultimately, children’s health outcomes.

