### Follow-up

Participants will be followed prospectively for 12 months after recruitment with measurements at baseline, 6 months, and 12 months (Figure 1). Using the REDCap database, they will be sent the follow-up questionnaires immediately following the baseline questionnaire and at the 6- and 12-month follow-ups. Refer to Figure 1 for the details of each measure.

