For *aim 4*, we will use multivariable logistic regression models to examine the effect of unmet social needs on ED visits (any vs none) and hospitalizations (any vs none), testing whether there is an interaction between medication adherence and unmet social needs in this relationship (whether better adherence is protective in children with unmet social needs). A similar approach will be used for asthma control using an ordinal regression model for the 4-point PPACI.

For *aim 5*, we will use descriptive statistics to document the prevalence of unmet social needs in our sample as well as within families and use logistic regression models to test whether referrals to social services modulate those trajectories.

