### Power Calculation and Feasibility

Previously published data using the asthma clinic database found a mean PPDC (our measure of adherence and primary outcome) of 68%, with an SD of 33% [24]. In previous studies, a 25% [102] or 1 SD difference [103] in adherence was associated with significant differences in the number of ED visits. As those studies used slightly different measures of adherence, we will be conservative and power our study to detect a 16% difference (half an SD) in PPDC between the participants above and below the median of scarcity and future discounting scores. Using 2-sample *t* tests (2-tailed), an α of .05, and a power of 0.8, this will require us to recruit 135 participants. Accounting for 30.4% (41/135) of missing data (covariates) and loss to follow-up, we will recruit 200 participants. The prevalence of unmet social needs in the clinical population is unavailable; however, in our patient population, 26.59% (335/1260) of children are from the lower quintile of the material deprivation index. In addition, recent Canadian data suggest a food insecurity prevalence of 29% among youth and young adults [104]. Assuming that 25% (50/200) of participants have at least one unmet social need, the proposed sample size will allow 85% power to detect a 16% difference (half an SD) in adherence between those with versus without unmet social needs.

On the basis of preliminary data from the asthma clinic, 87.68% (1139/1299) of patients who were prescribed daily controller medications consented to reMed. In another study ([name] et al, unpublished data, August 2023) from our clinic with a similar population and participant burden, 30% of eligible families consented to participate in the study. Using this ratio, we would need to approach approximately 670 families to obtain our desired sample size. There are at least three half-day clinics a week where recruitment could occur, with a minimum of 3 families per clinic. Using a conservative estimate, even if 29.9% (200/670) of families consent to participate, recruiting 200 participants will take 18 months.

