## Results

This study obtained funding in April 2021. The research activities of this study began in December 2021. Participant enrollment and data collection began in August 2022 and are expected to be completed in 24 months (August 2024). As of February 2023, 100 participants have been recruited and have completed all baseline data. Data analysis will begin once all participants have been recruited and follow-up measures (6-month and 12-month follow-up) are in progress. Primary results of the study are expected to be available in the first months of 2025.

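### Exploratory aim 5 asks about change over calendar time, but its stated analysis names no calendar term, and within-family change alone cannot be read as pandemic progression

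*Protocol article*

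**What the plan says.** Under Scientific Objectives, the second exploratory aim (aim 5 in the analysis section) is worded "Document the progression of unmet social needs as the world moves to the next phase of the COVID-19 pandemic". The Discussion likewise expects the study to document ongoing changes in unmet needs in the wake of the pandemic.

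The measurement clock belongs to each family. Follow-up states: "Participants will be followed prospectively for 12 months after recruitment with measurements at baseline, 6 months, and 12 months". The abstract says of unmet needs, scarcity and future discounting: "These variables will be measured at recruitment as well as at 6- and 12-month follow-ups".

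Enrolment is staggered. Power Calculation and Feasibility expects that "recruiting 200 participants will take 18 months". The Results section reports an August 2022 start, completion of enrolment and data collection in 24 months, and "As of February 2023, 100 participants have been recruited".

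The analysis given for aim 5 has two parts: "we will use descriptive statistics to document the prevalence of unmet social needs in our sample as well as within families", and then "use logistic regression models to test whether referrals to social services modulate those trajectories". Neither part mentions calendar date, period or enrolment date.

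**The concern.** The aim is about calendar time, while the data are organised by time since enrolment. The references to prevalence within families and to trajectories point towards change from one visit to the next.

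The article describes three things that can shift reported needs with time in study, whatever happens in the outside world:

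- **Referral.** Families with identified needs who want help are referred to a social worker (Main Predictors). Aim 2 tests whether referral improves unmet needs.
- **Loss to follow-up.** The sample size allows for 30.4% missing covariate data and loss to follow-up together, so the families answering at 12 months may differ from those at baseline.
- **Assistance.** The baseline questionnaire is completed on site with a research assistant. The follow-up questionnaires are emailed, with help offered if they are not returned within a week.

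If change by visit were taken as progression through the pandemic, an effect of being in the study could be reported as a period trend, or a real period trend could be hidden.

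**Working it through.** The plan states no figure for this point, so there is none to reproduce. The check is whether the stated analysis can separate the two time scales.

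**Inputs from the article.** Visits at 0, 6 and 12 months. 100 families in about six months (August 2022 to February 2023), so about 12 months for 200 at a constant rate. Enrolment and data collection finished in 24 months. 200 families. 25% with at least one unmet need (the assumption in the power section).

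**Assumptions.** Uniform accrual over 12 months. Linear effects of 0.5 percentage points per month, for illustration only.

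**1. Calendar windows.** With 12-month accrual, baseline visits fall in study months 0–12, 6-month visits in months 6–18 and 12-month visits in months 12–24. Each visit pools families seen up to 12 months apart, and neighbouring visits overlap by 6 months. This fits the 24-month timeline. An 18-month accrual would end at 18 + 12 = 30 months, which does not fit it, so the 12-month case is used here.

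**2. Separation within a family.** Completion date = enrolment date + time in study. Between two visits of one family the enrolment date cancels, so the two clocks move one for one. Let c be the calendar effect and s the in-study effect, per month. Expected prevalence at visit v is

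P(v) = 25 + c × (6 + v) + s × v,

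where 6 is the mean enrolment month. Hence P(12) − P(0) = 12 × (c + s). Only the sum c + s is recovered.

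| Scenario | c | s | P(0), P(6), P(12) | Change over 12 months |
|---|---|---|---|---|
| A: in-study effect only | 0 | −0.5 | 25, 22, 19 | −6 |
| B: calendar effect only | −0.5 | 0 | 22, 19, 16 | −6 |
| C: opposite effects | +0.5 | −0.5 | 28, 28, 28 | 0 |

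A and B show the same change. C hides a real calendar rise.

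**3. Plotting all visits by date is not enough.** The visit times 0, 6, 12 have variance 24. Uniform enrolment over 12 months has variance 12²/12 = 12. Time in study and calendar date therefore correlate at √(24/36) = 0.82. The pooled slope on date without a visit term is c + s × 24/36. In scenario A this is −0.5 × 0.667 = −0.33 points per month, although the true calendar slope is zero.

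**4. What can separate them.** Only the spread of enrolment dates between families. Baseline visits ordered by enrolment date return 0, −0.5 and +0.5 in A, B and C, provided that the type of family enrolled does not drift over time.

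**5. Precision.** The standard error of the baseline-only slope is √(0.25 × 0.75/200) / SD(enrolment date) = 0.0306 / (1/√12 year) = 0.0306 / 0.289 = 0.106, or 10.6 points per year. The 95% half-width is 1.96 × 10.6 = 20.8, about ±21 points per year. Using all three visits with a visit term and complete follow-up, the half-width would lie between 20.8/√3 = 12.0 (independent answers within a family) and 20.8 (identical answers). Dropout would widen this.

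**The case against.** The strongest reply is that the article does not commit to the analysis being criticised. It promises descriptive prevalence without fixing the time axis, and a condensed article may leave that to a fuller document. This stands in part. A reader might infer that prevalence will be tabulated by visit and any change credited to the pandemic, but the article says neither. What remains is that the article does state an analysis for aim 5, its terms describe change within families, and such change cannot answer the aim alone.

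A reader might also infer that referral is ignored. It is not. Aim 2 models referral and access to services as time-varying exposures, and aim 5 tests whether referral alters the trajectories. These models address one in-study influence. They do not deal with dropout or assistance, and they produce no calendar trend.

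Nor do the documents support a change of instrument between visits. Study Assessments puts the questionnaires on the same web platform throughout. Only place and assistance differ, and no figure shows that answers shift as a result.

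Finally, the remedy has limits. At about ±21 points per year, a change of 6 points per year would not be detected by the baseline-only check. Recruitment is stratified by deprivation quintile and age group, so if some strata fill earlier, the mix of enrolled families drifts with calendar time. Both objections stand and shape the fix.

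**Conclusion.** The concern holds as a mismatch between an exploratory aim and its stated analysis. Aim 5 is about calendar time, the analysis names no calendar term, and within-family change identifies only the sum of calendar and in-study effects. In the illustration that means an identical 6-point fall from two different causes, or no visible change when they oppose each other. Those effect sizes are assumed and are not estimates of bias in this study. The window and correlation figures assume uniform 12-month accrual.

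Severity is low. The aim is exploratory and largely descriptive, and the primary outcome, its analysis and the sample size are unaffected.

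**What to change.** State the time axis for aim 5 and make four changes:

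1. Describe the prevalence of unmet needs by calendar date of questionnaire completion as well as by visit.
2. Model the presence of any unmet need on calendar date and visit (baseline, 6, 12 months) as separate terms, with clustering by family and adjustment for the recruitment strata (deprivation quintile and age group).
3. As a check, report the trend across baseline visits by enrolment date with the same adjustment. These visits precede any study referral and are all completed on site. They cover only the enrolment window.
4. State that visit-to-visit change will not be attributed to the pandemic without this separation.

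The cost is analysis wording only, provided that completion dates are kept. The article does not say so, and this should be confirmed. The separated trend rests on differences in enrolment date between families and will be imprecise, so it should be reported as descriptive, with its interval.

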### Power Calculation and Feasibility

Previously published data using the asthma clinic database found a mean PPDC (our measure of adherence and primary outcome) of 68%, with an SD of 33% [24]. In previous studies, a 25% [102] or 1 SD difference [103] in adherence was associated with significant differences in the number of ED visits. As those studies used slightly different measures of adherence, we will be conservative and power our study to detect a 16% difference (half an SD) in PPDC between the participants above and below the median of scarcity and future discounting scores. Using 2-sample *t* tests (2-tailed), an α of .05, and a power of 0.8, this will require us to recruit 135 participants. Accounting for 30.4% (41/135) of missing data (covariates) and loss to follow-up, we will recruit 200 participants. The prevalence of unmet social needs in the clinical population is unavailable; however, in our patient population, 26.59% (335/1260) of children are from the lower quintile of the material deprivation index. In addition, recent Canadian data suggest a food insecurity prevalence of 29% among youth and young adults [104]. Assuming that 25% (50/200) of participants have at least one unmet social need, the proposed sample size will allow 85% power to detect a 16% difference (half an SD) in adherence between those with versus without unmet social needs.

On the basis of preliminary data from the asthma clinic, 87.68% (1139/1299) of patients who were prescribed daily controller medications consented to reMed. In another study ([name] et al, unpublished data, August 2023) from our clinic with a similar population and participant burden, 30% of eligible families consented to participate in the study. Using this ratio, we would need to approach approximately 670 families to obtain our desired sample size. There are at least three half-day clinics a week where recruitment could occur, with a minimum of 3 families per clinic. Using a conservative estimate, even if 29.9% (200/670) of families consent to participate, recruiting 200 participants will take 18 months.

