### Recruitment

We will recruit 200 families, stratified to recruit 40 families geographically from each quintile of the Pampalon material deprivation index [65-67]. Refer to the *Power Calculation and Feasibility* section for the method of determining the sample size. The Pampalon material deprivation index, measured at the level of the dissemination area and associated with the postal code of the child’s primary residence, is a composite of the (1) proportion of persons without a high school diploma, (2) employment:population ratio, and (3) average personal income obtained from the Canadian census [65,66].

Previous evidence suggests that adherence decreases with the age of the child, coinciding with responsibility for taking medication shifting from parents to their children as they age [53-59], whereas evidence for the impact of children’s sex is mixed [56,57,62,68,69]. We will stratify our recruitment to ensure equal recruitment between age groups (2-7, 8-12, and 13-17 years), and all analyses will consider the child’s age and sex [4].

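### The 85% power for the unmet-needs comparison counts all 200 families, although the same paragraph allows for 30.4% loss; with about 139 evaluable families it is about 69–72%

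*Protocol article*

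**What the plan says.** All the figures are in the Power Calculation and Feasibility section of the protocol article.

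- PPDC has a mean "of 68%, with an SD of 33"%.
- For scarcity and future discounting, split at the median, the target is a 16-point difference, described as half an SD. With two-sample *t* "tests (2-tailed), an α of .05, and a power of 0.8, this will require us to recruit 135 participants".
- The recruitment target follows: "Accounting for 30.4% (41/135) of missing data (covariates) and loss to follow-up, we will recruit 200 participants".
- For unmet social needs, the prevalence is said to be unavailable, and the claim reads: "Assuming that 25% (50/200) of participants have at least one unmet social need, the proposed sample size will allow 85% power to detect" a 16-point difference in adherence, again described as half an SD, between families with and without such needs.

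The abstract (Methods) names the comparison of PPDC between families with and without unmet social needs during the study period, by multivariate linear regression, as the primary analysis.

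**The concern.** The number 200 does two jobs in one paragraph. In the first calculation it is a recruitment target that already contains an allowance for families who cannot be analysed. In the second it is the analysed sample. Nothing in the section exempts the unmet-needs comparison from the loss just assumed.

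The comparison affected is the one the abstract calls primary. If its power is nearer 70% than 85%, the chance of missing a true 16-point difference is about 30% instead of 15%. A reader relying on the published figure would take a null result as stronger evidence of no association than it is. The power would also fall below the 80% the authors adopted for their other comparisons.

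**Working it through.** **Inputs** (Power Calculation and Feasibility): SD 33; difference 16 points, or 16.5 if half an SD is taken literally (16/33 = 0.485 SD); 25% exposed; loss 30.4%. The two-sided α of .05 is stated for the first calculation and carried over to the second.

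**Formula.** With n₁ exposed, n₂ unexposed and N = n₁ + n₂:

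- SE = 33 × √(1/n₁ + 1/n₂), noncentrality λ = difference/SE.
- Power = P(|T| > t₀.₉₇₅), with T noncentral *t* on N − 2 degrees of freedom and noncentrality λ.

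**Step 1: the 135.** For 16 points, SD 33, equal groups and 80% power, the normal approximation gives 67 per group (134) and the *t* distribution 68 per group (136). The 135 is reproduced, as a number of families analysed.

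**Step 2: the 85%.** With 50 and 150, SE = 33 × √(1/50 + 1/150) = 5.39. For 16 points λ = 2.97 and power is 84.0%; for 16.5 points λ = 3.06 and power is 86.1%. The stated 85% lies between the two and uses all 200 families.

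**Step 3: apply the stated loss.** 200 × (1 − 0.304) = 139.2, about 139 families, of whom 25% is 34.75 against 104.25. SE = 6.46; λ = 2.48 or 2.55; power 69.1% or 71.7%.

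**Step 4: other readings of the loss.** The 30.4% is written as 41/135, so its base is unclear: 135/(1 − 0.304) = 194 and 135 + 41 = 176, and neither is 200. The candidate samples at 25% exposed are:

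| Families analysed | Basis | Power, 16 points | Power, 16.5 points | Difference detectable with 80% power |
|---|---|---|---|---|
| 200 | no loss | 84.0% | 86.1% | 15.2 |
| 159 | 41 families lost from 200 | 74.9% | 77.4% | 17.0 |
| 139 | 30.4% of 200 lost | 69.1% | 71.7% | 18.2 |
| 135 | the number the first calculation needs | 67.8% | 70.5% | 18.5 |

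**Step 5: prevalence.** At 139 families, power for 16 and 16.5 points is 62.2% and 64.9% at 20% exposed, 73.1% and 75.7% at 29% (the food insecurity figure the section cites), and 79.4% and 81.8% at 40%.

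**Step 6: what 85% would take.** At a 25/75 split, 85% power needs 206 evaluable families for 16 points or 194 for 16.5. At 30.4% loss that means recruiting about 296 (206/0.696) or 279 (194/0.696).

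**The case against.** The strongest reply is that little may be lost from this comparison. PPDC comes from medical records and the pharmacy registry, and consent to the registry is an inclusion criterion. Unmet needs are first recorded on site with a research assistant, and the Results section reports complete baseline data for the first 100 families. An unadjusted comparison by baseline need could therefore keep nearly all 200 families, and 85% would then be close to right. This stands as a route to the stated figure. It does not support the figure as written: the allowance expressly includes missing covariates, the abstract specifies a multivariate model, and it defines need over the study period, which brings in the emailed 6- and 12-month questionnaires.

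A second reply is that 139 is only one reading of an unclear loss figure. That is fair, and the table shows the others. Apart from the no-loss case, none reaches 80% at 25% exposed.

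A third is that the prevalence of at least one need across several domains may well exceed 25%. It may, and power would rise; but the documents do not establish it, and the 85% is claimed at 25%.

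It is also true that the 200 was set by the scarcity and discounting calculation, so the sample size does not hang on this sentence.

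The section also cites 26.59% of clinic children in the lower deprivation quintile, whereas recruitment is "stratified to recruit 40 families geographically from each quintile", which makes that quintile 20% of the sample. This is peripheral: an area-level index does not fix the share of families reporting a need.

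**Conclusion.** The concern holds. The 85% is correct only if every recruited family is analysed, which conflicts with the loss assumed earlier in the same paragraph. Under that loss, power is about 69–72% with 139 evaluable families, some 14 points below the stated figure. It is 68–70% on the 135 the first calculation requires and 75–77% if only 41 families are lost.

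These figures assume SD 33, a two-sided two-sample *t* test, and 25% exposed among the families analysed as well as among those recruited. Heavier loss among families with unmet needs would lower power, and a prevalence above 25% would raise it. Covariate adjustment is not modelled, as in the protocol's own calculation. Because the figure is wrong as written and belongs to the named primary analysis, it should be corrected.

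**What to change.** Replace the unmet-needs power sentence with, for example: *With 139 evaluable families, of whom 25% have at least one unmet social need, power is about 69–72% to detect a difference of 16 to 16.5 points in PPDC; the difference detectable with 80% power is about 18 points.* Give the same figures for 20% exposed (62–65%) and 29% exposed (73–76%).

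Add that 85% holds only if no family is dropped, and state which families enter this comparison. If the authors intend to take exposure from the on-site baseline questionnaire and expect almost complete registry data, they can say so and justify a smaller loss; the power should then be given for that number. Also state whether the 30.4% is a fraction of those recruited or of the 135, since this decides between 139 and 159 evaluable families.

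The cost is one or two sentences and a less favourable published figure. No extra families and no change to the outcome or design are required.
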